#### Secondary outcomes

2.6.2

Personality will be assessed at baseline with the 100-item HEXACO-PI-R (Lee and Asthon, 2018) which measures 6 dimensions: Honesty-Humility, Emotionality, Extraversion, Agreeableness, Conscientiousness, and Openness to Experience. Each dimension is assessed with 16 items (e.g., “I often check my work over repeatedly to find any mistakes.”, “I am energetic nearly all the time.”, “Having a lot of money is not especially important to me.”), with the interstitial facet Altruism measured with 4 items. The six HEXACO dimensions have shown high reliability (range α = 0.82–0.89). Measuring personality enables personalized feedback in the first module of the application (see also Table 1).

Psychosocial wellbeing will be measured with the Warwick-Edinburgh Mental Wellbeing scale (Tennant et al., 2007), which is a broad measure of positive mental health. The questionnaire consists of 14 items (e.g., “Last week, I have been feeling relaxed.”; α = 0.84). The short 7-items version will be used for the interim measurements (Ng Fat et al., 2017).

Self-efficacy, referring to one's sense of competence to effectively deal with life stressors, will be assessed with the General Self-efficacy Questionnaire (Schwarzer and Jerusalem, 1995). The questionnaire consists of 10 items (e.g., “I can always manage to solve difficult problems if I try hard enough.”; range α = 0.75–0.91).

Self-esteem will be assessed with the Rosenberg Self-esteem Scale (Rosenberg, 1965) measuring people's global evaluation of themselves. The scale consists of 10 items (e.g., “On the whole, I am satisfied with myself.”; α = 0.86).

### Data management

2.7

All members of the research team have signed a confidentiality statement, are familiar with procedure to manage and store data (in line with the guidelines and procedures of the Ethics Board of the Institute of Education and Child Studies at Leiden University (ECWP2021-320)), and have access to the data. Data is collected online and will be stored on secured servers of Leiden University that are backed up regularly. To monitor data quality, attention checks will be incorporated in the questionnaires.

### Statistical analyses

2.8

Data will be analyzed on the basis of an intention-to-treat principle, meaning that participants will be included in the analyses regardless of whether they received the (complete) intervention or not. Depending on the analytical model, missing data will be handled either with Multiple Imputation (MI) or with Full Information Maximum Likelihood (FIML). Conditions will be compared at baseline to examine initial differences on age and gender. In case of differences between conditions, these variables will be controlled for in subsequent analyses.

Users' experiences and adherence to the intervention (aim 1) will be examined through the examination of usage data and user experience measures. The overall effectiveness of the intervention (aim 2) will be examined by comparing conditions on the primary and secondary outcomes (except for personality) using Analysis of Covariance (ANCOVA), with the baseline measure of the relevant outcome as covariate, and Latent Growth Curve (LGC) modeling. This enables us to examine differences between conditions immediately after the intervention and whether trajectories of change differ between conditions. To examine participants' change after each intervention module (aim 3), we will conduct repeated measures ANOVAs on the outcomes that are measured on a weekly basis, i.e., self-defeating behavior, future self-identification, and psychosocial wellbeing.

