### Participants and power calculation

2.2

Participants are first-year students enrolled in a university in the Netherlands who own an Android or iPhone smartphone. Sample size was determined by an a-priori power analysis with G*Power. Estimation of effect size is based on Tanner-Smith et al. (2018) who examined mean effect size distributions for universal interventions in a review of meta-analyses (Cohen's *d* ranging from 0.23–0.58). Assuming a significance level of *p* < .05, a medium effect size of Cohen's *d* = 0.50, two conditions, and one covariate, a sample size of 128 participants is estimated to achieve a power of 80%. Considering a drop-out rate of 20%, we aim to include 83 participants per condition, resulting in a total sample of 166 participants.

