### Recruitment and randomization

2.3

Participants will be recruited via the university's official communication channels (e.g., university website, social media). Additionally, flyers will be distributed in university buildings. Furthermore, student associations will be requested to distribute the study advertisement among their members. Finally, the study will be advertised during the university's introduction week for incoming students, and announced at lectures for first-year students.

Interested students can schedule an appointment for the intake session. At the beginning of the session, students are screened for eligibility. Eligible students are randomly assigned to one of the two conditions on a 1:1 ratio, using block randomization with blocks of 6 (i.e., within a block 3 participants are allocated to each condition), and proceed with the intake session.

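### Age and gender are adjusted for only if the randomised arms happen to differ on them, so chance imbalance rather than prognostic value decides whether they enter the models, and precision is lost

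*Protocol article*

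**What the plan says.** Section 2.8 (Statistical analyses) sets a two-step rule. First, "Conditions will be compared at baseline to examine initial differences on age and gender". Then, "In case of differences between conditions, these variables will be controlled for in subsequent analyses". The rule names no test, threshold or other criterion. It stands ahead of the analyses for aims 2 and 3 and so governs the ANCOVAs, the latent growth curve models and the repeated measures ANOVAs.

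One covariate is fixed in advance: the ANCOVA is run "with the baseline measure of the relevant outcome as covariate". Table 2 (section 2.6) shows no T1 value for weekly goal achievement, and academic results are obtained only at T4. Both are listed as primary outcomes in section 2.6.1.

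On allocation, section 2.3 states: "Eligible students are randomly assigned to one of the two conditions on a 1:1 ratio, using block randomization with blocks of 6". It mentions no stratification by age or gender. Nothing elsewhere in the article includes age or gender regardless of the comparison.

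**The concern.** After sound randomisation, a difference between the arms in age or gender is a chance event. Whether one is seen says nothing about whether the variable predicts the outcome, and prediction is the reason to adjust. The rule can therefore fail in two directions. A prognostic variable that happens to be balanced is left out, although including it would shrink the standard error. A variable with no prognostic value is added because it happens to differ.

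At stake are the precision of the between-arm comparisons and a model that can be written down before the data are seen. For weekly goal achievement and academic results, age and gender are the only covariates the plan names, so their whole covariate set depends on what the comparison shows.

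**Working it through.** **The plan's own figure.** Section 2.2 gives the inputs: "Assuming a significance level of *p* < .05", "a medium effect size of Cohen's *d* = 0.50", and "two conditions, and one covariate, a sample size of 128 participants is estimated to achieve a power of 80"%. For a two-arm ANCOVA, f = d/2 = 0.25, df1 = 1, df2 = N − 3 and noncentrality f²N. At N = 128 the noncentrality is 0.0625 × 128 = 8.0 and power is 0.801; at N = 127 it is 0.798. So 128 reproduces. (The recruitment target of 166 exceeds 128/0.8 = 160. That errs on the safe side and does not bear on this point.)

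**How often the rule fires.** Assume that a difference means p < 0.05 on each variable, with independent tests. The chance of at least one trigger under correct randomisation is 1 − 0.95² = 0.0975, about 10%. At p < 0.10 it is 1 − 0.90² = 0.19. So in about nine trials out of ten neither variable enters, however prognostic it is.

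**What that costs.** The simulation used N = 128 and 6,000 runs per scenario. These inputs are assumptions: baseline–outcome correlation 0.5; age and gender each correlated r with the outcome and independent of baseline; 70% in one gender category; trigger p < 0.05; d = 0.4 for power.

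| r | Power: never adjust | Power: conditional | Power: always adjust | Type I error: never / conditional / always |
|---|---|---|---|---|
| 0 | 0.737 | 0.736 | 0.733 | 0.054 / 0.053 / 0.052 |
| 0.2 | 0.735 | 0.737 | 0.780 | 0.053 / 0.050 / 0.049 |
| 0.4 | 0.734 | 0.751 | 0.927 | 0.049 / 0.037 / 0.049 |

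The rule fired in 9.4% to 10.1% of runs. A repeat of the simulation gave conditional power of about 0.75 against 0.78 at r = 0.2, 0.75 against 0.92 at r = 0.4, and a conditional type I error of about 0.04 at r = 0.4.

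**Check by hand.** The residual variance is 1 − 0.25 = 0.75 with baseline only, and 0.75 − 2r² with age and gender added: 0.67 at r = 0.2 and 0.43 at r = 0.4. The standard error of the arm difference is √(4 × variance/128):
- baseline only: √(3.00/128) = 0.153
- r = 0.2, always adjust: √(2.68/128) = 0.145
- r = 0.4, always adjust: √(1.72/128) = 0.116

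The simulated standard deviations of the estimate agree: 0.151 to 0.154, 0.144 to 0.147, and 0.117.

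**Share of the gain that the rule keeps.** At r = 0.4 it is (0.751 − 0.734)/(0.927 − 0.734) = 0.017/0.193, about 9%. At r = 0.2 it is (0.737 − 0.735)/(0.780 − 0.735) = 0.002/0.045, about 4%, which is within simulation error.

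**Direction of the error rate.** The simulation standard error at 0.05 is √(0.05 × 0.95/6000) = 0.0028. The conditional 0.037 lies (0.050 − 0.037)/0.0028, or about 4.6 standard errors, below nominal. The departure is real and conservative.

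**The case against.** The plan's defence has real content. The most useful covariate, the baseline outcome, is fixed in advance. Only two named variables are conditional, under a rule announced beforehand, and an article may leave the exact criterion to the full plan. All of that stands, and it limits the point to age and gender. It does not rescue the rule, because selection by imbalance is what the article itself prescribes, whatever criterion is used.

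Four stronger readings are tempting and are not supported:

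- **That covariates are selected by a significance test.** Section 2.8 speaks only of a comparison. The 10% rests on an assumed p < 0.05 trigger. A comparison by eye would still be data-driven, and less well defined.
- **That false positives increase.** The simulation shows no inflation; where the error rate moves, it falls.
- **That the estimate is biased.** With 83 per arm and the same assumed trigger, an age gap of up to 1.974 × √(2/83) = 0.306 SD would go unadjusted. At an assumed correlation of 0.3 that is 0.3 × 0.306 = 0.09 SD. But this is chance imbalance at the extreme edge in a single trial, which the standard error already covers, and not bias of the estimator. One standard error of the age gap is √(2/83) = 0.155 SD, or 0.3 × 0.155 = about 0.05 SD. If age correlates 0.3 with baseline as well, and baseline 0.5 with the outcome, ANCOVA removes half of the 0.09: 0.3 × 0.306 × (1 − 0.5) = about 0.046 SD.
- **That two teams must reach different models.** With a defined threshold they would agree. They can diverge only because no criterion is stated.

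Nor do the documents show that age or gender predicts these outcomes. Among first-year students age may vary little. If neither is prognostic, the three strategies perform alike. Never adjusting for them would also be a valid fixed rule.

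**Conclusion.** The point holds for age and gender. The plan selects these two covariates by chance imbalance, and the demonstrated harm is lost precision, together with an error rate that can fall slightly below nominal.

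Its size depends on assumptions that the documents do not settle: a p < 0.05 trigger and the strength of the two variables as predictors. Over outcome correlations from 0 to 0.4, the power forgone runs from nothing, through about 0.03 to 0.04 at 0.2, to about 0.17 to 0.18 at 0.4. The upper figures are generous, because the simulation takes age and gender to be unrelated to the baseline outcome. Where they are related, the fixed covariate already captures part of the gain. Weekly goal achievement and academic results have no such covariate, which is why the rule matters most there.

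This is worth correcting because the correction is almost free. It does not threaten the validity of the trial.

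**What to change.** In section 2.8, delete the conditional rule. State instead that every between-arm model includes age and gender, together with the baseline value of the outcome where one exists, and that baseline characteristics are reported by arm descriptively, without deciding the model. Make the change before outcomes are compared by arm.

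The cost is an edit of two sentences and about two degrees of freedom out of roughly 125 (128 − 3). Both variables are already to be compared at baseline, so no new data are needed. N = 128 is essentially unchanged: even when neither variable is prognostic, simulated power is 0.733 with adjustment always against 0.736 under the conditional rule, a difference within simulation error.

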We hypothesize that participants experience the smartphone application as user friendly and engaging, and use it multiple times per week. Furthermore, we hypothesize that the intervention is effective in increasing students' future self-identification, future-oriented mindset and behaviors (e.g., increasing future-orientation, reducing self-defeating behavior), and personal goal attainment. Regarding the effectiveness of the separate intervention modules, we hypothesize to see positive intervention effects after each module, given that all modules are based on theoretical mechanisms of change. It is important to note, however, that to the best of our knowledge, this is the first time these theories of change are combined and incorporated in a smartphone application, which, in turn, may affect the effectiveness of these theorized mechanisms.

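### Seven equally ranked primary outcomes serve one effectiveness aim, but the sample size and its 80% power are for a single ANCOVA at .05

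*Protocol article*

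**What the plan says.** Section 2.6.1 of the protocol article places seven between-arm measures under the primary heading: future orientation, self-defeating behavior, goal commitment, weekly goal achievement, future self-identification, academic results and impulsiveness. Engagement and user experience are under the same heading, but they are collected in the smartphone arm only and play no part in a comparison of arms.

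Section 2.8 addresses the effectiveness aim by "comparing conditions on the primary and secondary outcomes (except for personality) using Analysis of Covariance (ANCOVA"), with the baseline value as covariate, "and Latent Growth Curve (LGC) modeling". It gives the two methods different questions: the difference at the end of the intervention, and the difference in trajectory.

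Section 1.4 states one hypothesis spanning several outcomes: "we hypothesize that the intervention is effective in increasing students", followed by future self-identification, mindset and behaviors, and goal attainment.

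Section 2.2 gives the sample size: "Assuming a significance level of *p* < .05, a medium effect size of Cohen's *d* = 0.50", then "two conditions, and one covariate, a sample size of 128 participants is estimated to achieve a power of 80" percent. The effect size is not tied to a named outcome. The enrolment target is 166 after allowing for 20% dropout.

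Table 2 shows that academic results are collected only at T4 and that weekly goal achievement has no T1 value.

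**The concern.** The 5% and the 80% in section 2.2 describe one ANCOVA on one outcome. The effectiveness aim in section 2.8 rests on seven outcomes of equal rank, and the article does not say whether success means any of them, all of them or a particular one. The figures fit only the third case, and no outcome is named. Under an any-outcome reading, the chance of a false claim of effectiveness is well above 5%. Under an all-outcomes reading, or with a correction, the power can fall below 80%. If the main outcome or the deciding method is chosen after the data are seen, the choice cannot be repaired.

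**Working it through.** **Inputs.** Section 2.2: alpha .05, d = 0.50, two groups, one covariate, 128 analysable, 80% power, 20% dropout, 166 enrolled. Section 2.6.1: seven between-arm primaries. Table 2: five of these have T1 and T2 values. Assumed, because the article does not give them: a two-sided test, the correlation between outcomes (0 to 0.5), and the baseline-post correlation r (0, 0.5, 0.6).

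**1. Reproducing the plan's figure.** For an ANCOVA F test, f = d/2 = 0.25 and the noncentrality is f² × N = 0.0625 × 128 = 8.0, with 1 and 128 − 3 = 125 degrees of freedom. Power at .05 is 80.1%. At N = 127 it is 79.8%, so 128 is the minimum. A one-sided test would need only 101, so the stated figure is two-sided. It is the power of one test, with no credit for variance explained by the covariate.

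**2. Error if any one primary at .05 counts, under no true effect.** If independent, the error is 1 − 0.95^k. Correlated cases were simulated with equally correlated normal test statistics.

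| Tests | Independent | Correlation 0.3 | Correlation 0.5 |
|---|---|---|---|
| 7 (all between-arm primaries) | 1 − 0.95^7 = 30.2% | 27.2% | 23.0% |
| 5 (those with a T1 value) | 1 − 0.95^5 = 22.6% | 20.9% | 18.3% |

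These figures count one test per outcome. A second method adds further, highly correlated tests and would raise the error somewhat; that increase is not quantified here.

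**3. Power if all seven must succeed.** Alpha is protected, but power is about 0.80^7 = 21% if the outcomes are independent, and at most 80% however strongly they are correlated.

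**4. Power if the error is controlled, N = 128, d = 0.50.** A covariate with correlation r raises the noncentrality to 8.0/(1 − r²): 10.67 at r = 0.5 and 12.5 at r = 0.6. Bonferroni over seven uses .05/7 = .0071. Holm was simulated with the effect present on all seven outcomes and correlations of 0 to 0.5 between them.

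| Baseline-post r | Bonferroni, per outcome | Holm, average per outcome |
|---|---|---|
| 0 | 53.9% | about 66–68% |
| 0.5 | 70.1% | about 82–85% |
| 0.6 | 78.6% | about 89–92% |

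The Holm figures treat the test statistics as normal. With t statistics on 125 degrees of freedom they are about one point lower (65–66%, 81–84% and 88–91%). If fewer outcomes have a true effect, Holm power falls toward the Bonferroni column. Bonferroni over five gives 58.5% at r = 0.

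**5. Which outcomes can take the stated analyses.** Academic results have one time point, so they allow neither a baseline covariate nor a growth curve. Weekly goal achievement has no T1 value, so it allows no baseline-adjusted ANCOVA. Five primaries can take both methods as section 2.8 describes them.

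**The case against.** The strongest reply is that this is a condensed article, that the analysis plan is not shown, and that the choice of multiplicity adjustment is commonly left to that plan. This stands in part. A reader might infer that the trial will test every primary at .05 without correction, but the article does not say so: .05 appears only as a sample-size input, and section 2.8 neither states nor rules out an adjustment. What the article itself fixes is an unranked list of seven primaries beside a sample size for one test. An unseen adjustment would not by itself reconcile those two.

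A reader might also infer that each outcome is tested twice, giving 14 chances of a false positive. Table 2 does not allow this for two outcomes, and the two methods answer different questions with strongly correlated results. Section 2.2 also points to the ANCOVA as the powered analysis, although section 2.8 does not call it deciding. Counting the three parts of future self-identification to reach nine tests is likewise unsupported: Table 2 lists one eight-item concept, and no separate subscale tests are specified.

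Nor do the documents support saying that controlling the error always breaks the 80%. The 54% assumes Bonferroni and a covariate that explains nothing. Holm with r = 0.5 and effects on all seven outcomes stays above 80%. Enrolling 166 and losing 20% leaves 166 × 0.8 = 132.8 rather than 128, which helps slightly.

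Finally, no any-outcome rule is written, and the study also serves to develop the application. The 23–30% is therefore conditional on that reading. Even so, section 2.8 does test effectiveness, in a randomized trial sized for that purpose.

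**Conclusion.** The point holds as a mismatch between the primary outcomes and the sample size, and it should be fixed. The stated 5% and 80% are correct for one ANCOVA, but the article does not say which outcome that ANCOVA concerns or what result would count as effective. If any significant primary at .05 suffices, the family-wise error is 23–30% for seven outcomes, or 18–23% for the five with a T1 value, at assumed correlations of 0.5 down to 0. If the error is controlled, per-outcome power at 128 participants runs from 54% (Bonferroni, no covariate credit) to above 80% (Holm, r = 0.5 or more, d = 0.50 on all seven). Where the trial falls in that range depends on r and on how many outcomes truly change, and the article gives neither.

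**What to change.** Make these changes before outcome data are seen:

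- **Section 2.6.1.** Name one primary outcome with both T1 and T2 measures, for example future orientation at T2. Test it at .05 with the baseline-adjusted ANCOVA that section 2.2 powers, and make the other between-arm outcomes secondary under Holm. Alternatively, keep the outcomes as co-primary under Holm.
- **Section 2.8.** State that this ANCOVA decides the effectiveness aim and that the growth curves are supportive. Give a feasible comparison for academic results (T4 only) and weekly goal achievement (no T1), for example a comparison of arms without a baseline covariate.
- **Section 2.2.** State that 80% is the power of one unadjusted test. If co-primaries are kept, add the adjusted figure with the assumed r.

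The cost is wording in three sections and no added participants. With one named primary the stated 80% stands for that outcome. Outcomes made secondary, or adjusted as co-primaries, have less favourable stated power.

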## Abstract

**Background:**

Short-term mindsets interfere with the consideration of future consequences and therefore predict negative behaviors. We developed a smartphone-based intervention aiming to increase a future-oriented mindset and personal goal attainment by strengthening future self-identification and stimulating episodic future thinking. The aims of the study are 1) to examine users' experiences with the application and their treatment adherence, 2) to examine the effectiveness of the intervention, and 3) to explore which intervention modules generate the strongest changes in key outcomes.

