### FutureU: a smartphone-based intervention

1.3

Building on earlier research, FutureU aims to stimulate a future-oriented mindset and personal goal attainment by strengthening people's ability and motivation to consider their future and fostering their identification with their future self. The intervention consists of three modules, each lasting seven days. The first module focuses on future self-identification and personality, the second on temporal distancing and wise reasoning in decision making, and the third on stimulating a growth mindset (Dweck and Yeager, 2019) and goal achievement. By engaging with their future self on a daily basis, we expect participants to gain a more vivid and positive view of their future and to incorporate their future self into their own identity. This positive vivid image of the future self and its integration into one's identity is expected to foster future-oriented mindset and behaviors (e.g., future orientation, reduced self-defeating behaviors, psychosocial well being), and personal goal attainment (Nurra and Oyserman, 2018; Verplanken et al., 2008).

The intervention includes components that have been related to positive intervention effects in prior interventions. Goal setting, personalized feedback, and supportive messages are implemented throughout the intervention. Participants set goals both at the start of the intervention and on a weekly basis during the intervention. Personalized feedback and supportive messages, which are partially based on participants' responses in the application, are communicated via the future self, such as the advice they formulate for their present self from the perspective of their future self. Although the feedback and support messages are not provided by a therapist, automatically generated personalized support has been shown to generate equivalent effects (Linardon et al., 2019).

We use technology to create a persuasive three-dimensional visual analog, an ‘avatar’, of participants' future self, and create the suggestion of interaction with this future self. Moreover, we developed an interaction within the application, a ‘time travel portal’, intended to facilitate mental time travel and alternating between taking the perspective of the future self and that of the present self. Furthermore, the intervention is standardized, ensuring intervention fidelity, and stimulates engagement with the application through the use of daily push notifications.

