### The present study

1.4

The current study has three aims. First, we will examine users' experiences with the application and intervention adherence. This provides important information for the further development of the FutureU smartphone application, as high levels of acceptability and usability increases users' tendencies to apply the recommended intervention techniques (Sekhon et al., 2017). Second, we will analyze the overall effectiveness of the intervention. This will provide an indication about the extent to which the intervention is able to stimulate a future-oriented mindset, increase identification with the future self, promote beneficial behaviors, reduce self-defeating behavior, and foster personal goal attainment. Third, we will explore participants' change on several outcomes during the intervention to study the effectiveness of each module. We specifically focus on concepts in which changes can be measured over the course of a week, such as self-defeating behaviors (e.g., missing classes or work, overspending, procrastinating) and psychosocial wellbeing. Studying change on key outcomes after each module allows for determining which modules carry most promise for establishing change. This information provides detailed insights into how the intervention can be developed further to improve effectiveness and carries theoretical relevance (Fanning et al., 2017).

Given that interventions aimed at changing behavior are best implemented during a transformational life event and change of context (Dai et al., 2014; Verplanken et al., 2008), the target population of the current study is first-year university students. For many of these students transitioning from secondary school to university involves moving to a new city, living by themselves, being separated from family and close others, and/or taking on new roles. During transformational life events, people are more inclined to take a ‘big-picture’ view of their lives, which may motivate behavioral changes (Dai et al., 2014). Additionally, a change of context can alter choices and decisions based on contextual information in order to adapt to the new situation (Verplanken et al., 2008).

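### Aim 3 (exploratory) treats week-by-week change as module effectiveness, but the stated ANOVA names no condition term, and the single fixed order means the modules cannot be ranked.

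*Protocol article*

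**What the plan says.** The abstract (Background) gives aim 3 as "to explore which intervention modules generate the strongest changes in key outcomes". Section 1.4 describes it as exploring "change on several outcomes during the intervention to study the effectiveness of each module" and adds: "Studying change on key outcomes after each module allows for determining which modules carry most promise for establishing change". The same section states a directional expectation: "we hypothesize to see positive intervention effects after each module". The abstract's Discussion says that what is learned about the modules will feed further development of the app.

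Section 2.8 gives the analysis: "To examine participants' change after each intervention module (aim 3), we will conduct repeated measures ANOVAs". The main clause of that sentence reads in full "we will conduct repeated measures ANOVAs on the outcomes that are measured on a weekly basis", and it lists three outcomes: self-defeating behavior, future self-identification and psychosocial wellbeing. The sentence on aim 2 is different in kind. There, effectiveness "will be examined by comparing conditions on the primary and secondary outcomes".

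On the design, section 1.3 says: "The intervention consists of three modules, each lasting seven days". Table 1 ties module 1 to week 1, module 2 to week 2 and module 3 to week 3. Section 2.3 randomizes students to one of two conditions, not to modules or module orders. Under sections 2.1 and 2.5.2, controls are assessed at matching time points and also set weekly goals.

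**The concern.** Two separate problems arise.

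**Control contrast.** Only the app arm receives modules, so change after a module, taken literally, is a within-arm quantity. Such a change mixes the module's effect with whatever would have happened that week anyway: the course of the first university term, repeated completion of the same questionnaires, and weekly goal setting. Section 2.5.2 says the active control exists so that effects beyond goal setting can be seen. An analysis of change without a condition term gives that up for aim 3.

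**Fixed order.** Every app participant meets the modules in the same sequence. A difference between the week 1 and week 3 changes could reflect module content, novelty, accumulated exposure, or a delayed effect of an earlier module. The data contain nothing that separates these.

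At stake is the advice drawn for developing the app. A module could look strong or weak because of when it was delivered.

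**Working it through.** **The plan's own figure.** Section 2.2 gives N = 128 for d = 0.50 (f = 0.25), alpha 0.05, two conditions, one covariate and 80% power. The noncentral F calculation with df = 1 and N − 3 and noncentrality N·f² gives power 0.801 at N = 128, so the figure reproduces. Allowing for 20% drop-out, 128/0.8 = 160; the planned 166 is above that. The sample size serves the aim 2 comparison and is not at issue. No figure is given for aim 3.

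**Inputs for the illustration.** 83 per arm with 20% drop-out (section 2.2) leaves 83 × 0.8 = 66.4 per arm. The waves are T1, two interims and T2 (Table 2). The between-wave correlation and the size of any shared drift are not in the article. Both are assumptions.

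**Step 1: a shared drift in a within-arm analysis.** For a paired change in SD units, SE = √(2(1 − r)/n).

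| Assumed r | SE | Three-week change, 0.45 SD | One-week change, 0.15 SD |
|---|---|---|---|
| 0.7 | √(0.6/66.4) = 0.095 | z = 4.7 | z = 1.6 |
| 0.6 | √(0.8/66.4) = 0.110 | z = 4.1 | z = 1.4 |

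A drift of 0.15 SD per week in both arms thus gives a clear total change in the app arm with no intervention effect. No single week's change reaches 1.96, and a constant drift adds the same amount to each week.

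**Step 2: simulation over a range.** 4,000 runs per setting, 66 completers per arm, r = 0.6, no intervention effect, same trend in both arms. Share of runs with p < 0.05:

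| Shared trend | Within-arm time test | Condition by time |
|---|---|---|
| none | 5% | 5% |
| 0.05 SD/week | 20% | 6% |
| 0.10 SD/week | 65% | 4% |
| 0.15 SD/week | 96% | 5% |
| 0.20 SD/week | 100% | 5% |
| week 1 step of 0.1 SD | 12% | 5% |
| week 1 step of 0.2 SD | 44% | 5% |
| week 1 step of 0.3 SD | 81% | 5% |

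The condition-by-time test removes the shared trend. Both are overall tests over four waves; neither compares one module with another.

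**Step 3: what a control contrast still cannot do.** Let m1, m2, m3 be the modules' own effects and c12, c13, c23 the effect of having had an earlier module on the change in a later week. The between-arm differences in weekly change then estimate:

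- week 1: m1
- week 2: m2 + c12
- week 3: m3 + c13 + c23

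That is three estimable quantities for six unknowns, before any novelty or fatigue term. Setting every c to zero would identify the modules, but with one order the data cannot test that assumption.

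**Step 4: wellbeing.** Table 2 and section 2.6.2 give 14 items at T1 and T2 and 7 at the interims. The week 1 change runs from 14 to 7 items and the week 3 change from 7 to 14. Only the week 2 change and the overall T1–T2 change stay within one form, so a four-wave analysis needs a common scoring.

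**The case against.** The strongest reply is that the missing condition term is inferred from silence in a condensed article. Section 2.8 names a test family and does not say that it is confined to the app arm. Table 2 marks only app engagement and app experiences as intervention-arm measures, so the interim data cover both arms. Section 2.8 also promises intention-to-treat analysis and adjustment of later analyses for imbalance in age or gender. A fuller plan may contain condition by time. This stands in part: a reader might infer that the controls are definitely excluded, and the article does not support that. But its wording leaves the within-arm reading open, and its contrast with the aim 2 sentence invites it.

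Second, the latent growth curve models compare trajectories between conditions. They are assigned to aim 2, however, the article does not say whether the interim waves enter, and they cannot separate module from week.

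Third, a reader might take the drift figures as evidence that one module would be falsely favored. They are not: constant drift treats all weeks alike, the z of 4.7 concerns the total change, and the week 1 step was judged only by an overall time test.

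Fourth, aim 3 is labelled exploratory, and no rule for selecting modules is stated. That lowers the severity. It does not rescue the section 1.4 claim, because the fixed order is a feature of the design that no analysis plan can remove.

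**Conclusion.** The point holds, at moderate severity. As worded, the aim 3 analysis leaves open an uncontrolled reading in which shared change passes as a module effect. Whatever the analysis, the statement in section 1.4 that the data allow the most promising modules to be determined is wrong for a design with one module order.

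The first part rests on the article's wording and would fall away if a fuller plan specifies condition by time. The second part needs no assumption beyond Table 1 and the two-condition randomization. Rejection rates of 20% to 100% depend on assumed drifts of 0.05 to 0.20 SD per week and r = 0.6; they illustrate the mechanism and do not forecast this trial. A reader might also infer that the trial's effectiveness conclusion is undermined. It is not: aim 2 compares randomized conditions and its sample size reproduces.

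**What to change.** 1. In section 2.8, state that the aim 3 models for the three weekly outcomes use both arms, with condition, time (categorical: T1, interim 1, interim 2, T2) and condition by time. The planned ANOVA is enough; a mixed model is an option. Report the between-arm difference in each week's change with a 95% CI.
2. Score wellbeing on the items common to both forms at all four waves. This assumes that the 7 items are contained in the 14, which the article does not state. If no common scoring is possible, limit its weekly contrasts to waves that used the same form.
3. In the abstract (Background and Discussion) and section 1.4, replace the claim about the most promising modules with the increment over control in the week each module was delivered, given the preceding modules. Say that modules cannot be ranked independently of their order.

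The control data are already planned, so the cost is analysis and wording. The price is a more modest claim and wider intervals. With equal arms the SE of a weekly contrast rises by √2: at r = 0.7 from 0.095 to 0.134 SD, and the 95% half-width from 0.19 to 0.26 SD. At r = 0.6 the half-width goes from 0.22 to 0.30 SD.
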